#### Shedding criteria

After inclusion, the treatment was not completed according to the planned protocol;Serious adverse events occur during the treatment and, hence, cannot continue;The patient’s symptoms worsened, and it was not suitable to continue participating in the trial.

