### Modifications{11b}

The study allows participants to exit voluntarily, or they may be removed by study clinicians if they experience negative effects related to the study or meet the shedding criteria during the treatment. If a participant leaves due to negative effects, the study clinicians will assess if they need further treatment. Safety data will be collected for all participants who leave the study. Patients from both groups may receive additional treatment after their exit. Patients who experience severe pain and cannot tolerate MUA therapy or show no improvement within a short period of time, impacting their quality of life and sleep, should receive emergency medication such as the use of painkillers, muscle relaxants, or other medications which are deemed absolutely necessary for the participant’s well-being and then be removed from the trial.

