### Participant timeline {13}

Patients with FS will be randomly divided into the trial group and the control group. All patients included in this study will receive their disseminated treatment on Day 1 and undergo a program of shoulder exercises, for 2 weeks. The relevant data will be collected before the intervention, 1 day, 2 weeks, 4 weeks, 12 weeks, and 24 weeks after the intervention, while safety evaluations and adverse events will be recorded each visit. The specific participant’s timeline is shown in Table 1.

**Table 1 Tab1:** Participant’s timeline

Timepoint (state unit)	−7~0 DAY	Treatment day	1 day	2 weeks	4 weeks	12 weeks	24 weeks
Visit number:	1	2	3	4	5	6	7
Enrollment:							
Eligibility screen	x						
Informed consent	x						
Allocation	x						
Imagining examination	x						x
Baseline questionnaire	x						
Interventions:							
Intra-articular steroid injection		x					
Manipulation under anesthesia		x					
2-week shoulder exercises			x	x			
Assessments:							
Active range of motion		x	x	x	x	x	x
Passive range of motion		x	x	x	x	x	x
CMS		x	x	x	x	x	x
MPQ		x	x	x	x	x	x
VAS		x	x	x	x	x	x
PPI		x	x	x	x	x	x
Total effectiveness rate							x
Safety evaluation		x					x
Adverse event		x					x

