### Blinding (masking)

#### Blinding mechanism {17a}

Due to the nature of the intervention, comparing MUA and intra-articular injection treatment options, it is not possible to blind the clinicians to the allocation of treatment. However, they are strongly advised not to reveal the participant’s allocation status during follow-up assessments. An employee outside the research team will enter data into separate datasheets to ensure that the researchers who are responsible for the analyzation of the data do not have access to the information about allocation. The assessments of clinical recovery will be carried out by an experienced clinician who has undergone extensive training and is blind to treatment allocation.

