## Statistical methods

### Outcomes {20a}

The data will undergo encoded analysis and various patient details, such as their baseline information, range of motion, CMS, VAS, MPQ, PPI, duration of symptoms before treatment, and past histories, will be compared and summarized between the groups. The outcome variables of all patients will also be summarized by treatment group and time, following descriptive statistics such as the number of patients, mean and standard deviation (or median and interquartile range) for continues variables, and relative frequencies for categorical variables. The number of participants included in each analysis will be reported, and we will adhere to the intention to treat principle regarding the group assignment.

Differences between the various treatments will be calculated using one-way ANOVA statistics; the follow-up data of each group will be statistically analyzed using ANOVA of repeated measures if they conformed to normal distribution and chi-square, and if they do not, the rank sum test will be used; logistic regression will be used to analyze the correlation between each treatment method and the efficacy. The study will categorize complications by types, such as infection, post-operative pain, nerve, blood vessel, tendon, or bone injury, and count them overall. Poisson regression analysis will be used with corrections for overdispersion when appropriate. The impact of treatment on complication rates will be expressed as MUA to intra-articular injection rate ratios. The safety of the treatment will be evaluated by identifying and summarizing any adverse events that occur during the study. All treatment effects will be reported with their 95% confidence intervals and *p*-values. The statistical analysis will be conducted using the IBM SPSS statistical package (version 25.0).

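### Patients rescued for poor response are removed from the trial before the week-24 primary assessment, partly on a trigger that only MUA patients can meet

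*Protocol article*

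**What the plan says.** Modifications {11b} sets a conduct rule. Patients in severe pain who "cannot tolerate MUA therapy or show no improvement within a short period of time", with an effect on quality of life and sleep, are to receive emergency medication for their "well-being and then be removed from the trial". The same section opens with a wider rule: "they may be removed by study clinicians if they experience negative effects related to the study or meet the shedding criteria during the treatment". For those who exit it promises one kind of data: "Safety data will be collected for all participants who leave the study". Additional treatment after exit is allowed in both groups.

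One of the Shedding criteria is that the patient's "symptoms worsened, and it was not suitable to continue participating in the trial".

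In Participant timeline {13}, the Table 1 row "Total effectiveness rate" has a single mark, in the 24-week column. On who knows the allocation, Blinding mechanism {17a} says "it is not possible to blind the clinicians to the allocation of treatment". On analysis, Outcomes {20a} says "we will adhere to the intention to treat principle regarding the group assignment".

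Two sections soften the rule. Concomitant care {11d} and Analysis population and missing data {20c} both ask that, after dropout or poor compliance, whatever assessments are still feasible be carried out. Concomitant care {11d} also allows the same drugs for intolerable pain with recording only, and mentions no removal.

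**The concern.** The removal is tied to outcome. Failure to improve early is close to the Ineffective category of the primary outcome in Outcomes {12}, so the rule can take likely failures out of follow-up before they are scored. Early removal precedes week 24, the only visit at which the total effective rate is assessed.

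Three features make this worse than ordinary drop-out:

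- Inability to tolerate MUA cannot occur in the steroid arm, so one trigger acts on one side of the comparison.
- The time allowed for improvement is undefined, and unblinded clinicians make the decision.
- Removal serves little treatment purpose. The main treatment is given on one day, and only 14 days of exercise follow.

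Analysing patients in their assigned group does not supply a week-24 result for someone who was not examined. An analysis plan can choose how to score the gap, but it cannot recover the examination.

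**Working it through.** **Inputs.** Sample size {14}: 160 per arm, response rates pT = 0.862 and pC = 0.428, drop-out allowance 10%. The planned difference is 0.862 − 0.428 = 0.434. The protocol gives no share r of patients removed without a week-24 status, so r = 0.05 (8 per arm) and r = 0.10 (16 per arm) are assumptions. The second sets r equal to the whole drop-out allowance.

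**The plan's own figure.** With these rates, 80% power and two-sided 0.05, the pooled two-proportion formula gives 18 per group, or 20 after 10% drop-out, not 160. That mismatch is a separate matter. Here it only explains why power is not the issue.

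**Bounds.** These assume that assessed patients show pT and pC, and nothing about how removed patients would have fared.

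Both arms lose a share r:
- lower = (1−r)pT − [(1−r)pC + r]
- upper = [(1−r)pT + r] − (1−r)pC

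Only the MUA arm loses a share r:
- lower = (1−r)pT − pC
- upper = (1−r)pT + r − pC

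| Removal | r | Lower | Upper |
|---|---|---|---|
| Both arms | 0.05 | 0.95×0.434 − 0.05 = 0.362 | 0.95×0.434 + 0.05 = 0.462 |
| Both arms | 0.10 | 0.90×0.434 − 0.10 = 0.291 | 0.90×0.434 + 0.10 = 0.491 |
| MUA only | 0.05 | 0.819 − 0.428 = 0.391 | 0.391 + 0.05 = 0.441 |
| MUA only | 0.10 | 0.776 − 0.428 = 0.348 | 0.348 + 0.10 = 0.448 |

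**Compared with sampling error.** With 144 assessed per arm, the 95% margin is 1.96 × √(0.862×0.138/144 + 0.428×0.572/144) = 0.0985, or 9.9 points. At r = 0.10 in both arms the half-width of the bounds is (0.491 − 0.291)/2 = 0.10. The gap in follow-up could add about as much uncertainty as sampling does.

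**Power.** The worst case at r = 0.10 is 0.90×0.862 = 0.776 against 0.90×0.428 + 0.10 = 0.485. With 160 per arm the standard error is √[(0.776×0.224 + 0.485×0.515)/160] = 0.0515. Then 0.291/0.0515 − 1.96 ≈ 3.7, so power is above 99.9%.

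**When the sign is open.** With removal in both arms, the lower bound falls below zero when the difference among assessed patients is less than r/(1−r). That is 0.053 at r = 0.05 and 0.111 at r = 0.10.

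**Direction.** Suppose instead that 0.862 and 0.428 are the true rates, and that a share q of non-responders is removed and left out of the denominator. The observed rate is then p/[p + (1−p)(1−q)]. With q = 0.25 in both arms this gives 0.893 − 0.499 = 0.393 (from unrounded rates), a smaller difference. With q = 0.25 in MUA only it gives 0.893 − 0.428 = 0.465, a larger one. Both q and the exclusion are assumptions; the example shows only that the bias can go either way.

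**The case against.** The strongest reply is that loss of week-24 data is inferred, not stated. Concomitant care {11d} and Analysis population and missing data {20c} tell staff to contact patients who drop out and complete what can be completed, which could include week 24. That softens the point. But neither section commits a removed patient to the week-24 visit, and {11b} both removes the patient and promises only safety data.

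Second, the Constant–Murley score, the other primary outcome, is measured from day 1 onward, as are motion and pain. Values up to removal therefore exist and an analysis plan could use them. This is true, but they are not week-24 status.

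Third, the MUA-specific trigger needs severe pain as well as intolerance of a one-day procedure under a nerve block, so it may catch few patients. This also stands; nothing in the protocol gives the number.

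Fourth, the intention-to-treat statement concerns group assignment, and no section drops removed patients from the denominator. The rule therefore works against the principle without strictly contradicting the sentence. Likewise, recording rescue drugs in {11d} and removing the patient in {11b} are not a strict contradiction, but they leave an overlapping patient's status unclear.

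Fifth, the bounds are extreme. The lower one counts every removed MUA patient as a failure and every removed steroid patient as a success. If all removed patients were failures in both arms, the difference at r = 0.10 would be 0.90 × 43.4 = 39.1 points. The bounds show what would be unknown, not what is expected.

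**Conclusion.** The concern holds. Followed as written, {11b} removes patients for poor response before the only scheduled assessment of the total effective rate, and one of its triggers exists in the MUA arm alone. The resulting bias has unknown direction and size, since early non-improvers may still improve by week 24. If 5% to 10% of each arm went unassessed, and assessed patients showed the planned rates, the difference could not be fixed more closely than 36.2 to 46.2 points (5%) or 29.1 to 49.1 points (10%). A benefit as large as planned would survive this. The sign would be in doubt only if the difference among assessed patients were below 5.3 points (5%) or 11.1 points (10%). The removal shares are assumptions. The rule should be changed because it governs conduct, and later analysis cannot repair assessments that were not made.

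**What to change.** In Modifications {11b}:
- Delete the instruction to remove rescued patients.
- Make the intolerance trigger refer to the allocated treatment instead of MUA.
- Extend the data promise for those who leave from safety to safety and efficacy.
- In the opening sentence, have clinicians stop further allocated treatment instead of removing the patient.
- Add: *Rescue medication is recorded with drug and dates. Patients who receive it, who stop for negative effects or who meet a shedding criterion are followed at every visit through week 24 in the assigned arm, unless consent is withdrawn. Stopping treatment does not end follow-up.*

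In the Shedding criteria, reword the worsening item so that it concerns continuing the allocated treatment, not participation in the trial.

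The scoring of rescued patients and the denominator can be left to the analysis plan, with a sensitivity analysis that counts rescue as failure.

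The cost is wording plus the remaining visits, reimbursed at 50 yuan each (Adherence {11c}). A patient removed just after day 1 has four visits left (weeks 2, 4, 12 and 24), or 200 yuan. For 10% of 320, that is 32 × 200 = 6,400 yuan in reimbursement. The downside is that the week-24 rate will include any effect of rescue drugs, which may change the difference between arms; the sensitivity analysis shows by how much.

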### Adherence {11c}

Due to the nature of this study, since the main treatment is done all at one time, its adherence is guaranteed. The follow-up time points in this study are 1 day, 2 weeks, 4 weeks, 12 weeks, and 24 weeks after the patients receive the treatment. Because of the physical examination involved, all follow-up time points must be completed by the patients at the hospital's outpatient or inpatient departments. The study staff will contact participants over the phone or on WeChat to supervise their home exercise program and to make appointments before their scheduled follow-up examinations. Finally, participants will receive reimbursement for their time and transportation as 50 yuan for each visit.

### Concomitant care {11d}

The care of a patient awaiting surgery may involve administering pain relief medication to alleviate discomfort, providing guidance on how to properly take care of the affected arm (e.g., weight bearing on the upper limbs), and offering general advice on preventing additional stiffness in the limb. This will not include a specific home exercise program, as it is considered as an active intervention. After the surgery, the use of painkillers, muscle relaxants, and other medications is prohibited during the trial period. However, if there are specific circumstances such as intolerable pain, emergencies or unforeseen medical conditions, and any other situation, deemed necessary by the treating physician to ensure the patient's health, where these drugs are absolutely necessary, they must be accurately recorded on the medication registration form. Patients who had pre-existing medical conditions before enrollment will continue with their initial treatment, and any medication administered for pain relief will be noted in the medication record form. If a patient drops out of the trial or has poor compliance, the detailed reasons for this will be recorded in the case observation form, and efforts will be made to contact the patient frequently to obtain their understanding and support. Any efficacy-related measures that can be completed will be recorded, and the final treatment time will be noted. The patient’s compliance and adverse reactions will be described statistically and compared between the two groups.

### Ancillary and post-trial care {30}

Both MUA (manipulation under anesthesia), intra-articular injection, and physical exercises are routine treatments for frozen shoulder (FS) in these three hospitals. Therefore, post-trial care, which includes ongoing treatment for a frozen shoulder, is accessible to all trial participants. If a trial participant wishes to make a formal complaint, they are suggested to do this through the Medical Affairs Office in the respective hospital. If patients experience severe postoperative complications, are harmed due to research personnel’s negligence, or encounter other adverse events, they will receive appropriate medical treatment, including surgical intervention if necessary. After treatment, a satisfactory compensation plan will be discussed with the patients. If they are still not satisfied, they may have grounds for legal action against the hospital and the researchers.

### Outcomes {12}

#### Primary outcome measures

##### Comprehensive efficacy evaluation (total effective rate)

Assessment was made primarily with reference to measurements of external range of motion of the glenohumeral joint and improvement in pain.

The specific judgment is as follows:①Cured: Shoulder pain disappears, forward flexion>150°, abduction>120°, extension>45°, and internal and external rotation>60°.②Effective: Shoulder joint pain basically disappears, with forward flexion from 120° to 150°, extension from 30° to 45°, abduction from 90° to 120°, and external and internal rotation from 45° to 60°.③Improved: Shoulder pain is reduced, and the range of motion is increased compared with that before treatment, but there is still limitation of movement.④Ineffective: no change in indications and symptoms before and after treatment.

The total effectiveness rate = (cure + effective + improved) / number of patients × 100%

#### Constant–Murley Score (CMS)

The CMS provides an assessment of both Individual parameters and clinical symptoms, which is sufficiently sensitive to reveal even small changes in function [51]. The score consists of four domains [52]: pain (15 points), activities of daily living (20 points), movement (40points), and strength (25points). The patients self-assess the pain and the first three questions of activities of daily living, and all other items are examiner assessed.

#### Secondary outcome measures

##### Active and passive range of motion (ROM)

The forward flexion, abduction, and external rotation, in both active and passive modes, are measured by a goniometer(measuring range: 0–360°, resolution: 0.05°) . The smallest unit of measurement is 5°. Forward flexion and abduction are measured in the standing position, external rotation measured with the arm post or held at the side, and the elbow in 90° flexion. Internal rotation is estimated to which height the patient can reach on his back with the tip of the thumb, recorded in both active and passive. The vertebra level of the sacrum is recorded as 1 point. From the fifth to first lumbar vertebra, it is numbered serially 2–6 and so on.

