### Eligibility criteria {10}

#### ***Inclusion criteria*** [49]

Age 40–70 years old [50]Meet the diagnostic criteria for shoulder coagulation, with significantly limited shoulder range of motion (less than 100° in forward flexion, less than 10° in external rotation, and less than L5 level in internal rotation) [12] and an MRI diagnosis of rotator cuff injury (conducted by professional radiologists from the Imaging Department).Voluntarily participate in this experiment and sign the informed consent

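### The internal rotation score has no value below the sacrum although entry requires internal rotation below L5, so in the mode used at entry the baseline is the minimum score or unscorable

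*Protocol article*

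**What the plan says.** Two places in the Protocol article bear on this.

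- **Eligibility criteria, Inclusion criteria.** Shoulder motion must be limited in three directions. The last two limits are "less than 10° in external rotation, and less than L5 level in internal rotation". The criterion does not say whether active or passive motion is meant.
- **Secondary outcome measures, Active and passive range of motion (ROM).** The method is stated as: "Internal rotation is estimated to which height the patient can reach on his back with the tip of the thumb". The result is "recorded in both active and passive" mode. The key then reads "The vertebra level of the sacrum is recorded as 1 point. From the fifth to first lumbar vertebra, it is numbered serially 2–6 and so".

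Table 1 schedules active and passive range of motion on the treatment day and at 1 day, 2, 4, 12 and 24 weeks. The Statistical methods section compares range of motion between groups at baseline. It plans a repeated-measures ANOVA, or a rank sum test, for the follow-up data. The Additional analyses section also relates active and passive mobility to the degree of cuff injury.

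**The concern.** The entry rule and the scoring key meet at the same point. Entry selects patients who cannot reach L5. The key offers one score below L5 and stops there. The trial therefore recruits patients into the part of the scale that has least resolution, or none.

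Three things are at stake for internal rotation in the entry mode:

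- The baseline carries no information. It is a constant among scored patients, so a baseline comparison or a correlation with cuff injury can show nothing.
- Movement within the unscored region is lost in both directions. The patients affected are those with the least internal rotation.
- Patients who stay below the sacrum after treatment have no score of their own. They are either given 1, together with patients who truly reach the sacrum, or left missing.

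**Working it through.** There is no stated figure to reproduce, because no sample size or error rate depends on this item. The check is to place the entry limit on the scoring key.

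**Inputs.** Entry limit: below L5 (Inclusion criteria). Key: sacrum = 1, L5 = 2, L4 = 3, L3 = 4, L2 = 5, L1 = 6, rising from there (ROM section). I assume the entry limit is judged by the same thumb-height method. The protocol does not name buttock and lateral thigh; I use them as examples of positions short of the sacrum.

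**Step 1: score of each position.**

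| Position reached | Meets entry limit? | Score in the plan | Score on a key extended downward |
|---|---|---|---|
| Lateral thigh | yes | none | 0 |
| Buttock | yes | none | 1 |
| Sacrum | yes | 1 | 2 |
| L5 | no | 2 | 3 |
| L4 to L1 | no | 3 to 6 | 4 to 7 |

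The possible baseline values in the entry mode are 1 or no value. The open ending of the numbering rule cannot supply lower codes, because the numbers start at 1 at the sacrum and rise.

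**Step 2: what a change records.** Where the plan has no score, assume the assessor either enters 1 or leaves a blank.

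| Change | Recorded under the plan | Recorded on the extended key |
|---|---|---|
| Buttock to sacrum | 1 − 1 = 0, or missing | 2 − 1 = +1 |
| Buttock to L5 | 2 − 1 = +1, or missing | 3 − 1 = +2 |
| Sacrum to L5 | 2 − 1 = +1 | 3 − 2 = +1 |
| Sacrum to buttock | 1 − 1 = 0, or missing | 1 − 2 = −1 |
| L3 back to L5 | 2 − 4 = −2 | 3 − 5 = −2 |

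Gains from the sacrum upward, and relapse after such a gain, are recorded correctly. Only movement that starts or ends below the sacrum is lost or shortened.

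**Step 3: effect on the comparison between arms.** Let d be the number of levels a patient is below the sacrum (0 if at or above it). If such patients are entered as 1, recorded score = true score + d. At a given visit:

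recorded difference (MUA − injection) = true difference + [mean d in MUA − mean d in injection].

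At baseline, mean d is equal in the two arms in expectation because of randomization, so flooring at baseline cancels. At follow-up the bracket is zero if the arms have the same mean d. If the injection arm recovers less, the bracket is negative and shrinks a difference in favour of MUA. The documents give no value of d for either arm at any visit, so the bracket cannot be evaluated. If patients below the sacrum are left blank instead, they drop out of the analysis, and the loss again depends on how many there are in each arm.

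**The case against.** The strongest case against has five parts.

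1. **One mode only.** A reader might infer that every eligible patient starts on the floor in both modes. The documents do not support this. If the L5 limit was applied to active motion, passive internal rotation could start at 2 or more. Table 1 also places the baseline measurement on the treatment day, after a screening window of up to 7 days, so a repeat reading could differ slightly from the one that qualified the patient. This stands, and the point is limited accordingly.

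2. **Worsening is largely visible.** A reader might infer that deterioration cannot be recorded at all. That is too broad. Relapse after a gain is scored. Flexion, abduction and external rotation are measured by goniometer, and the Constant-Murley Score, the pain scales, adverse events and the 24-week imaging are all collected. Only internal rotation falling below the sacrum is lost.

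3. **No measurable bias.** A reader might infer a definite understatement of the treatment effect. Flooring at baseline balances in expectation. The share of patients below the sacrum is nowhere stated, and if nearly all entrants reach the sacrum the loss is close to nil. This stands: the effect may exist, but its size is unknown.

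4. **Small role.** This is one of four motions in a secondary outcome. The total effective rate states its rotation thresholds in degrees, the Constant-Murley Score has its own movement domain, and the sample size does not rest on this score. This also stands.

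5. **Condensed text.** A case report form or operating procedure might hold a code for patients who cannot reach the sacrum. That is possible. However, the article does not merely omit detail: it states where the numbering starts, and that start collides with its own entry limit. This part softens the point without removing it.

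**Conclusion.** The point holds in a limited form. As written, the scoring key gives an eligible patient a baseline internal rotation of 1, or no score, in whichever mode the entry limit refers to. Gains from below the sacrum up to it and deterioration below it go unrecorded. Patients who remain there at follow-up are pooled at 1 or missing. This may reduce the sensitivity of internal rotation to a difference between arms. Gains to L5 and above are still measured.

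No size can be given for the loss. It depends on how many patients in each arm are below the sacrum, and how far below, at each visit. The conclusion rests on two assumptions: that the entry limit and the outcome are measured in the same way, and that no unseen form adds a lower code. Neither primary outcome nor the sample size is put in doubt. The point is a correctable defect in one secondary measure.

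**What to change.** Add ordered categories below the sacrum to the ROM section and the case report form. One example is 0 = lateral thigh, 1 = buttock, 2 = sacrum, 3 to 7 = L5 to L1, and upward from there. Use the same key at baseline and at every visit, for active and passive motion. State in the inclusion criteria which mode the existing L5 limit refers to; the limit itself need not change.

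The cost is one line of scoring text and one form field, with no extra visit or procedure. Because recruitment began on 1 January 2023, existing records need recoding. On the example key, values at L5 and above shift by a fixed +1 (2 becomes 3, 6 becomes 7). A record coded only as 1, or left blank, can be recoded only where the level actually reached was noted. Where it was not, that information is lost, and the number of such records should be reported by arm and visit.
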